## Abstract

**Background:**

Echocardiography (ECHO) is a type of ultrasonographic procedure for examining the cardiac function and morphology, with functional parameters of the left ventricle (LV), such as the ejection fraction (EF) and global longitudinal strain (GLS), being important indicators. Estimation of LV-EF and LV-GLS is performed either manually or semiautomatically by cardiologists and requires a nonnegligible amount of time, while estimation accuracy depends on scan quality and the clinician’s experience in ECHO, leading to considerable measurement variability.

**Objective:**

The aim of this study is to externally validate the clinical performance of a trained artificial intelligence (AI)–based tool that automatically estimates LV-EF and LV-GLS from transthoracic ECHO scans and to produce preliminary evidence regarding its utility.

**Methods:**

This is a prospective cohort study conducted in 2 phases. ECHO scans will be collected from 120 participants referred for ECHO examination based on routine clinical practice in the Hippokration General Hospital, Thessaloniki, Greece. During the first phase, 60 scans will be processed by 15 cardiologists of different experience levels and the AI-based tool to determine whether the latter is noninferior in LV-EF and LV-GLS estimation accuracy (primary outcomes) compared to cardiologists. Secondary outcomes include the time required for estimation and Bland-Altman plots and intraclass correlation coefficients to assess measurement reliability for both the AI and cardiologists. In the second phase, the rest of the scans will be examined by the same cardiologists with and without the AI-based tool to primarily evaluate whether the combination of the cardiologist and the tool is superior in terms of correctness of LV function diagnosis (normal or abnormal) to the cardiologist’s routine examination practice, accounting for the cardiologist’s level of ECHO experience. Secondary outcomes include time to diagnosis and the system usability scale score. Reference LV-EF and LV-GLS measurements and LV function diagnoses will be provided by a panel of 3 expert cardiologists.

**Results:**

Recruitment started in September 2022, and data collection is ongoing. The results of the first phase are expected to be available by summer 2023, while the study will conclude in May 2024, with the end of the second phase.

**Conclusions:**

This study will provide external evidence regarding the clinical performance and utility of the AI-based tool based on prospectively collected ECHO scans in the routine clinical setting, thus reflecting real-world clinical scenarios. The study protocol may be useful to investigators conducting similar research.

**International Registered Report Identifier (IRRID):**

DERR1-10.2196/44650

## Introduction

### Background

Echocardiography (ECHO) is a type of ultrasonographic scan used for examining the cardiac function and morphology [1]. Due to the practicality of image acquisition, relatively low cost, and little-to-no-risks for the patient, ECHO remains the most widely used cardiac imaging examination [2]. Of pivotal importance for patient evaluation is the assessment of the left ventricular (LV) systolic function [3], with recommended evaluation parameters being the ejection fraction (EF) and global longitudinal strain (GLS) [4]. EF is the percentage of blood ejected from the ventricle in each contraction, measured as the ratio of stroke volume (difference between end-diastolic and end-systolic volume) over the end-diastolic volume. GLS describes the myocardial deformation across the ventricular longitudinal axis, measured as the relative length change of the ventricular myocardium between end-diastole and end-systole.

Estimation of LV-EF and LV-GLS from ECHO scans is performed by cardiologists either manually or semiautomatically using a dedicated software [5]. One or more cardiac cycles and apical views of the LV can be used in the estimation of both parameters. Different apical views (typically 4-chamber, 2-chamber, and apical long axis views) are obtained by different placements of the ultrasound probe relative to the heart apex [1]. The estimation process is usually laborious and time-consuming, especially when considering medical emergencies, while accuracy depends on the cardiologist’s experience in ECHO and the quality of scans [6], leading to considerable measurement variability [4,7]. Improving measurement precision and reliability is necessary, as it has been shown that EF and GLS values and their impairments are closely connected to patients’ prognosis and course [8,9].

Deep learning [10], the most recent advancement in artificial intelligence (AI), has revolutionized computer vision over the past decade. Deep neural networks can be trained on annotated images without the need for feature engineering and perform fully automated image analysis. Inevitably, deep learning–based systems have been used in medical imaging, with a recent surge in applications for cardiovascular imaging [11]. Such advanced AI and associated software could support cardiologists of various levels of expertise in LV function assessment with the automatic and more accurate estimation of LV-EF and LV-GLS, and at the same time reduce the time of ECHO examination and the variability of measurements. In conjunction with point-of-care ultrasonography, such AI-based assistance may significantly improve relevant case management in demanding health care settings, such as emergency departments.

### Objectives

This study aims at evaluating the clinical performance and producing preliminary evidence regarding the utility of a trained AI-based tool that automatically estimates LV-EF and LV-GLS from transthoracic ECHO scans. Two study phases are planned. The specific primary and secondary objectives of each study phase are listed in Textbox 1.

Primary and secondary objectives of the 2 phases of the study.
**Phase 1**
Primary objectiveDetermine if the automatic estimation of left ventricular ejection fraction and left ventricular global longitudinal strain from echocardiography scans by the artificial intelligence–based tool is noninferior in terms of accuracy to semimanual estimations by cardiologists of different experience levels.Secondary objectiveEvaluate the time required for left ventricular ejection fraction and left ventricular global longitudinal strain measurement from echocardiography scans by the artificial intelligence–based tool and by semimanual estimations of cardiologists of different experience levels.
**Phase 2**
Primary objectiveDetermine if the combination of the cardiologist and the artificial intelligence–based tool is superior to the routine examination practice of the cardiologist in terms of correct diagnosis of left ventricular function (normal or abnormal) based on examination of echocardiography scans, accounting for the cardiologist’s level of experience.Secondary objectiveEvaluate the time required for diagnosis with and without the assistance of the artificial intelligence–based tool.Evaluate the usability of the artificial intelligence–based tool based on cardiologists’ feedback after use.

## Methods

### Study Design

This is a prospective cohort study conducted in 2 phases, involving multireader, multicase diagnostic measurement, and diagnostic performance evaluation. Data (ECHO scans) collection is common between the 2 phases. The specific objectives of each study phase were detailed in Textbox 1. In both phases, reference measurements and reference diagnoses will be provided by a panel of 3 highly experienced cardiologists, via a collective intelligence process. We will proceed with the second phase if and when the AI-based tool is proven to be noninferior in terms of (at least) LV-EF estimation compared to (at least) low- and medium-experienced cardiologists in the first phase. Figure 1 provides an overview of the study.

**Figure 1 figure1:**
[figure not shown]
Study overview. After enrollment in the study, an ECHO scan will be acquired from each participant. In total, 120 scans are planned to be collected, with 60 scans used in the first phase of the study evaluating the performance of the AI-based tool in LV-EF and LV-GLS estimation compared to the semimanual estimation by cardiologists of different experience levels and the rest in the second phase evaluating the utility of the AI-based tool in LV function diagnosis by cardiologists of different experience levels. AI: artificial intelligence; ECHO: echocardiography; EF: ejection fraction; GLS: global longitudinal strain; HE: high experience; ICC: intraclass correlation coefficient; LE: low experience; LV: left ventricle; ME: medium experience.

### Clinical Site

The study will be conducted in the Third Cardiology Department of the Aristotle University of Thessaloniki (AUTH) in the Hippokration General Hospital, Thessaloniki, Greece. The hospital is equipped with a dedicated laboratory for ECHO acquisition (ECHO laboratory).

### Participants

ECHO scans will be acquired from 120 participants (data collection participants) referred for transthoracic echocardiography as part of routine clinical practice in Hippokration Hospital. In total, 15 cardiologists will be involved in the study (serving as comparators in phase 1), divided into three groups according to the relevant level of experience: (1) the low experience (LE) group will include residents of cardiology with ECHO experience of fewer than 5 years, (2) the medium experience (ME) group will include cardiologists with ECHO experience of more than 5 and less than 10 years, and (3) the highly experienced (HE) group will include cardiologists with more than 10 years of experience or certification in echocardiography from the European Association of Cardiovascular Imaging (EACVI) or the National Cardiac Society.

A panel of 3 expert cardiologists (reference panel) with more than 10 years of experience and certification in echocardiography from the EACVI or the national cardiac society, not participating in the HE group, will provide the reference measurements and diagnoses.

### Recruitment

Data collection participants will be recruited in the Third Cardiology Department of the Hippokration General Hospital. In particular, participants referred for transthoracic ECHO as part of routine clinical practice, including all possible diagnoses except those constituting exclusion criteria, will be invited to participate in data collection. Cardiologists serving at the Third Cardiology Department of the Hippokration General Hospital will be invited to participate in the examination of acquired echocardiograms.

### Inclusion and Exclusion Criteria for ECHO Acquisition

Participants eligible for data collection must meet the following criteria: (1) female or male, (2) older than 18 years, and (3) participants must be in sinus rhythm during the examination.

Participants will be excluded from data collection and processing based on the following criteria: (1) presence of atrial fibrillation, (2) presence of sinus or other tachycardia (heart rate>100 bpm), (3) presence of pacing rhythm, (4) complex congenital heart disease, (5) myocardial hypertrophy, (6) need for a contrast agent to improve echocardiographic resolution, (7) bad imaging quality with 2 or more myocardial segments not viewed in each apical view, and (8) incapability of providing full consent.

### Duration

The study is expected to last for approximately 2 years. The study is estimated to complete the enrollment of participants for data collection and of cardiologists within 6 months from initiation. However, enrollment in both cases will remain open until the study goal is met. Each cardiologist is expected to complete the tasks of both study phases in a maximum of 18 months. The second phase will only begin if and when the tool is proven to be noninferior in (at least) LV-EF measurement accuracy compared to (at least) the LE and ME groups of cardiologists in the first phase.

### Data Collection

#### Enrollment of Data Collection Participants and ECHO Scan Acquisition

Participants referred to the Third Cardiology Department of the Hippokration General Hospital for cardiovascular examination including ECHO (see “Recruitment” section) and deemed eligible for data collection will be invited to participate in the study. Enrollment in the study and ECHO scan acquisition will be performed on the same day. Participants will first review the study information sheet and undergo informed consent. Once consented, participants will be assigned a coded identification number. Afterward, basic demographics, anthropometrics, and vital signs (age, gender, height, weight, and blood pressure), as well as relevant medical history (known cardiovascular conditions), will be recorded. ECHO acquisition will follow the standard clinical practice. All ECHO scans will be performed at the Hippokration Hospital ECHO laboratory, by 1 experienced cardiologist with EACVI certification in ECHO. Scans will be acquired using the GE Vivid S5 ultrasound system (GE Healthcare) or the Clarius PA HD ultrasound scanner (Clarius Mobile Health Corp). Three views (a 2-chamber, a 3-chamber, and a 4-chamber apical view) will be acquired per scanning procedure, with 3 cardiac cycles per view. Views will be reviewed for diagnostic quality, and if a view does not meet the criteria set, the acquisition will be repeated.

#### Enrollment of Cardiologists

Cardiologists serving at the Hippokration Hospital will be invited to participate in the study. Cardiologists will first review the study information sheet and undergo informed consent. Once consented, they will be assigned a coded identification number. Demographics (age and gender) and experience, including career stage and experience in ECHO, will be recorded. Each cardiologist will be assigned to 1 of the 3 experience groups (LE, ME, and HE) according to the self-reported experience in ECHO.

#### Reference Measurements and Diagnoses

Acquired scans will be independently examined by the highly experienced cardiologists of the reference panel, who will estimate LV-EF and LV-GLS and provide a binary diagnosis of LV function (normal or abnormal) for each case. Examination of scans by the reference panel will take place on a single, dedicated computer (also referred to as a workstation) in the ECHO laboratory of the Hippokration Hospital. Cardiologists will examine scans in batches on different days, depending on their availability.

LV-EF and LV-GLS will be estimated using the same methods and standards applied in routine clinical practice. A commercially available speckle-tracking software (EchoPAC version 202.0, GE Healthcare) will be used. LV-EF will be estimated using the biplane Simpson method [4] from 2 and 4-chamber apical views after cardiologist-adjusted tracing of the LV cavity. For LV-GLS, the 2-dimensional speckle-tracking method [7] will be used. For each captured view, the cardiac cycle with the best image quality will be first selected out of the 3 captured cycles. If the image quality is similar among all 3 cycles, the intermediate one will be selected. To reduce bias due to user interaction, the beginning and end of the cardiac cycle will be the time points that will be automatically defined by the software, usually based on automatic QRS detection on the echocardiogram. In the second step, the endocardial border will be traced, and a region of interest will be constructed. Manual adjustments will be made after visual inspection of the segmental tracking results throughout the cardiac cycle, to obtain the best possible tracing of all myocardial segments. The peak systolic strain value per view, as automatically provided by the software, will be noted. Finally, LV-GLS will be calculated as the average peak strain of the 3 apical views.

Regarding LV-EF and LV-GLS, the reference measurement for each scan will be the average of measurements estimated by the 3 cardiologists, provided that there is a <20% discrepancy between the measurements. Regarding LV function, the reference diagnosis will be the majority diagnosis among the 3 equally weighted diagnoses, that is, at least 2 out of the 3 cardiologists of the reference panel arrived at this diagnosis. For cases where there is a discrepancy of ≥20% between at least 2 of the 3 LV-EF and LV-GLS measurements provided by the reference panel, the 3 cardiologists will examine them and estimate the reference measurements together.

#### Phase 1: Processing of ECHO Scans for LV-EF and LV-GLS Measurement

Out of the 120 ECHO scans to be acquired, the first 60 scans will be used for assessing the noninferiority of the AI-based tool in measuring LV-EF and LV-GLS.

Processing of scans by the AI-based tool will take place on the dedicated computer of the ECHO laboratory. For each scan, the AI-based tool will output an LV-EF and an LV-GLS measurement, along with the time required for producing both measurements. All 3 values will be recorded.

Comparator cardiologists of the 3 experience groups will independently examine each scan and estimate the LV-EF and LV-GLS. LV-EF and LV-GLS will be estimated using the same software and semimanual methods as in the case of the reference panel. For each scan, the LV-EF and LV-GLS values will be recorded along with the time required for estimation. The time required for estimation is defined as the time (in minutes) that elapsed from the moment a scan is loaded by the software until both measurements are estimated.

Cardiologists will examine scans in batches on different days, during working hours, and depending on their availability. A schedule with time slots will be communicated to them based on which they will be able to indicate their availability for the examination of each batch. Examination of scans will take place at the dedicated workstation of the ECHO Lab. At the end of phase 1, all 60 scans are expected to be processed by each cardiologist.

#### Phase 2: Examination of Scans for LV Function Diagnosis

In phase 2, the second batch of 60 scans will be used for assessing the superiority of the combination of the cardiologist and the AI-based tool in terms of LV function diagnosis from ECHO scans. Cardiologists of the 3 experience groups will independently examine batches of ECHO scans with and without the AI-based tool, and for each case, they will be asked to provide a binary diagnosis of LV function (normal or abnormal) based on visual inspection of the echocardiogram and measurements of LV-EF and LV-GLS. The decision will be recorded along with the time required to arrive at the diagnosis. For scans examined with AI assistance, cardiologists will use the AI-based tool that will allow them to view scans and automatically produce LV-EF and LV-GLS measurements. For scans examined without AI assistance, cardiologists will use the same software for viewing and estimating LV-EF and LV-GLS as in phase 1. For each cardiologist, ECHO scans reviewed with AI assistance will be different from those reviewed without AI assistance.

Before examining phase 2 cases, each cardiologist will be presented with materials describing how to use the AI-based tool and they will be given the opportunity to practice using the tool with 2 sample cases (independent of the study cases).

Examination of scans will take place on the same workstation of the ECHO laboratory as in phase 1, via scheduled time slots. At the end of phase 2, each cardiologist is expected to review and provide a diagnosis for 30 scans with AI assistance and 30 without AI assistance. Cardiologists that will examine at least 10 scans with AI assistance will be asked to complete the Greek version of the system usability scale (SUS).

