##### Secondary Outcomes

The following secondary outcomes will be produced in phase 1: (1) a Bland-Altman plot of LV-EF measurements produced by the AI-based tool with respect to reference measurements; (2) Bland-Altman plots of LV-EF measurements produced by LE, ME, and HE cardiologists with respect to reference measurements; (3) a Bland-Altman plot of LV-GLS measurements produced by the AI-based tool with respect to reference measurements; (4) Bland-Altman plots of LV-GLS measurements produced by LE, ME, and HE cardiologists with respect to reference measurements; (5) intraclass correlation coefficient (ICC) of LV-EF measurements produced by the AI-based tool with reference measurements; (6) ICCs of LV-EF measurements produced by LE, ME, and HE cardiologists with reference measurements; (7) ICC of LV-GLS measurements produced by the AI-based tool with reference measurements; (8) ICCs of LV-GLS measurements produced by LE, ME, and HE cardiologists with reference measurements; (9) time required by the AI-based tool for producing LV-EF and LV-GLS measurements from an ECHO scan; and (10) time required by LE, ME, and HE cardiologists for producing LV-EF and LV-GLS measurements from an ECHO scan.

#### Phase 2

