### Statistical Analysis Plan

#### Sample Size

The sample size of this study was determined based on realistic recruitment goals and comparability to the sample sizes of similar landmark studies [12,13]. In total, the study will recruit 120 individuals and each one will undergo a single ECHO examination. Half the scans will be used for phase 1 and the rest for phase 2. In total, 15 cardiologists, approximately 5 per experience group (LE, ME, and HE), will be recruited and participate in both study phases.

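### AI-versus-reference agreement on EF and GLS is planned on 60 scans although all 120 get panel reference values; phase 2 values should be recorded and used in a secondary analysis

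*Protocol article*

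**What the plan says.** **Reference values.** The Protocol article, Reference Measurements and Diagnoses, has the panel work through the acquired scans without limiting this to phase 1: "Acquired scans will be independently examined by the highly experienced cardiologists of the reference panel, who will estimate LV-EF and LV-GLS". The rule for combining readings is also per scan: "the reference measurement for each scan will be the average of measurements estimated by the 3 cardiologists" (provided the readings agree closely enough; otherwise the panel re-measures jointly).

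**Scans.** Under Sample Size, 120 people have one scan each, and "Half the scans will be used for phase 1 and the rest for phase 2". The phase 1 section reserves the earlier half for measurement: "the first 60 scans will be used for assessing the noninferiority of the AI-based tool in measuring LV-EF and LV-GLS".

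**What is recorded.** In phase 1 the tool's EF, GLS and run time are recorded, and so are each reader's EF, GLS and time. In phase 2 the tool supplies EF and GLS on assisted readings, and readers estimate both in the phase 1 software on unassisted readings. The recording sentence there reads: "The decision will be recorded along with the time required to arrive at the diagnosis". EF and GLS are not mentioned.

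**Outcomes.** Absolute error is the phase 1 primary outcome. The agreement outcomes, such as "a Bland-Altman plot of LV-EF measurements produced by the AI-based tool with respect to reference measurements" and the matching ICCs, are phase 1 secondaries. Phase 2 has agreement with the reference diagnosis (primary), then time to diagnosis and the usability score (secondary). Statistical Analyses keeps the same division.

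**The concern.** The stated aim is external validation of EF and GLS estimation. The article also concedes, under Strengths and Limitations, that the sample size did not come from a full power analysis. Against that background, three things are lost.

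1. **Precision.** The panel's measurements on the second 60 scans, the costly part of an agreement study, feed no listed measurement outcome.
2. **An estimate not selected by the gate.** Phase 2 runs only if phase 1 shows noninferiority on at least EF. Given progression, the phase 1 accuracy estimate tends to be optimistic. The second 60 scans play no part in that decision and could check it.
3. **Explanation of the phase 2 result.** The diagnosis rests on visual inspection together with EF and GLS. Without the values the reader had in hand, a missing benefit cannot be traced, case by case, to a wrong tool value or to a correct value that was not followed.

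The timing matters for the third item. Tool output can be regenerated later if the scans are kept. A reader's EF and GLS that were never captured cannot be recovered by any later analysis plan.

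**Working it through.** **Counts stated in the plan.** 120 / 2 = 60 scans per phase. Phase 1: 15 readers × 60 scans = 900 readings. Phase 2: 15 × 30 = 450 readings per condition. These are consistent. No SD, margin, alpha or power is given, so there is no precision or power figure to reproduce.

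**Coverage by phase, as the article lists it**

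| | Phase 1 scans (60) | Phase 2 scans (60) |
|---|---|---|
| Panel EF/GLS | yes | yes |
| Tool EF/GLS produced | yes, each scan | yes, on assisted readings |
| Reader EF/GLS produced | yes | yes, on unassisted readings |
| EF/GLS named as recorded | yes | no |
| Error, Bland-Altman, ICC listed | yes | no |

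**Precision of agreement.** In units of the SD of the tool-minus-reference differences, 95% half-widths are:

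- bias: t(n−1) / √n
- each limit of agreement: t(n−1) × √(1/n + 1.96² / (2(n−1)))

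For n = 60, t = 2.001:
- bias: 2.001 / √60 = 0.258
- limit: 2.001 × √(0.01667 + 3.8416/118) = 2.001 × 0.2219 = 0.444

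For n = 120, t = 1.980:
- bias: 1.980 / √120 = 0.181
- limit: 1.980 × √(0.00833 + 3.8416/238) = 1.980 × 0.1564 = 0.310

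Ratio for the limit: 0.310 / 0.444 = 0.70, so about 30% narrower. The phase 2 scans alone (n = 60) have the same precision as phase 1, 0.444 SD.

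**In points (the SDs are assumptions)**

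| Assumed SD of differences | Limit half-width, n = 60 | n = 120 |
|---|---|---|
| EF 4 | 1.78 | 1.24 |
| EF 6 | 2.66 | 1.86 |
| EF 8 | 3.55 | 2.48 |
| GLS 1.5 | 0.67 | 0.46 |
| GLS 2.0 | 0.89 | 0.62 |
| GLS 2.5 | 1.11 | 0.77 |

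**ICC (one-way model, two measurements per scan, exact F interval; ICC values are assumptions).** At 0.8 the 95% interval is 0.69 to 0.88 with 60 scans and 0.73 to 0.86 with 120. At 0.9 it is 0.84 to 0.94 and 0.86 to 0.93.

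**How many tool values phase 2 yields.** The article does not say how scans are allocated to readers and conditions. If every reader had the same 30 assisted scans, the readings would give only 30 new tool values, so n = 90 and a limit half-width of 0.359 SD. Reaching 120 for certain requires running the tool on all 60.

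**The case against.** The strongest reply is that nothing here is wrong. Each phase's outcomes match its objective: measurement in phase 1; diagnosis, time and usability in phase 2. The article does not say that nothing but the decision and time is recorded, and form fields and supportive analyses may sit in a fuller document. Doubling n narrows any interval by roughly this much, no stated precision target is missed, and no primary inference changes. All of that stands, and it limits the point to an improvement. What remains is that the article itself lists the recorded items and the outcomes by phase, and on that listing the second 60 scans contribute nothing to agreement.

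Stronger readings that a reader might draw are not supported:

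- *AI assistance is judged only on a binary call.* Time to diagnosis is compared by a superiority test and usability is scored. Only the accuracy of assisted reading is reduced to normal/abnormal.
- *The phase 2 values go unused.* Readers base their diagnoses on them. They are unused as outcomes, and their recording is not stated.
- *The effect of AI on measurement error cannot be learned.* On assisted readings the tool generates EF and GLS and no reader editing is described, so assisted error is largely the tool's error. Tool against reader, by experience group, is already the phase 1 primary comparison.
- *Sixty further tool-reference pairs are certain to arise.* The unstated allocation means they are not.
- *A 120-scan analysis is simply better.* It would include phase 1 data that exist alongside phase 2 data only because phase 1 succeeded. Adjusting for phase does not remove that.

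**Conclusion.** The point holds as a missed use of data, not as a contradiction or an arithmetic error. As listed, AI-versus-reference agreement rests on 60 scans while 120 have panel values, and the accuracy of assisted reading is assessed only through a binary diagnosis.

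The gain is about 30% narrower intervals for bias and limits of agreement. For a limit of agreement that is 0.44 to 0.31 SD, or about 2.7 to 1.9 EF points at an SD of 6, with the SD assumed because the article gives none. It also provides an estimate from 60 scans that the gate did not select.

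This assumes that the phase 2 values are not already captured under a fuller document and that the tool is run on every phase 2 scan. The phase 1 noninferiority test and both phases' primary outcomes are unaffected.

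**What to change.** 1. Keep the phase 1 gate and all primary outcomes on their own 60 scans.
2. Run the tool on all 60 phase 2 scans, whatever the allocation to readers, and record its EF and GLS.
3. For every phase 2 reading, in both conditions, record the EF and GLS the reader used. Enter them outside the timed interval, so that time to diagnosis is not inflated.
4. Prespecify, as a secondary end-of-study analysis, AI-versus-reference Bland-Altman and ICC for EF and GLS on (a) the phase 2 scans alone and (b) all 120 scans. State that (b) includes phase 1 data conditioned on success.
5. Do not add assisted-versus-unassisted EF/GLS error as a secondary outcome. If it is reported, label it exploratory, because it largely repeats the phase 1 tool-versus-reader comparison.

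**Cost:** two fields per phase 2 reading, at most 60 separate tool runs, and one further use of analyses already planned for phase 1. No new participants or panel readings are needed. The recording fields must be in place before phase 2 reading begins.
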